### Sample size calculation

In our 2020/21 pilot study, recruitment and intervention was conducted in male and female participants, separately. Participants were assessed at baseline and 3 months post intervention. Comparing the proportions of moderate/severe MDE (having a PHQ-9 score of 15+) (31) between baseline and 3-months, the proportion of MDE in the male intervention group reduced from 15.7 to 6.2% (-9.5%), whereas the proportion in the male control group increased from 10.8 to 12.7% (+ 1.9%). The proportion in the female intervention group changed from 12.8 to 14.5% (+ 1.7%), whereas the proportion in the female control group increased from 7.4 to 17.1% (+ 9.7%). However, the increase in depressive symptoms in female intervention group (1.9%) was not statistically significant. The slight increase may be due to the fact that the pilot was conducted during the height of COVID-19 when females were more emotionally affected [47, 48]. It does not mean that the intervention is harmful as compared to the increase in the control group; it may be an indication that the intervention helped maintain the mental health of females during the pandemic, whereas the mental health of those in the control group deteriorated significantly. In the post pandemic era, we expect that females who are in the intervention group will have a lower risk of MDE than those in the control group.

Assuming the 12-month incidence of MDE in female intervention and control groups is 1.7% and 9.7%, respectively, α = 0.05 and β = 0.80, G*Power calculation [49] indicates that at least 262 female participants are needed at baseline (131 in each group). Assuming the response rate over 12 months is 80% as we achieved in our previous trial [33], 330 female participants should be recruited. We also plan to examine the moderation effect by self-efficacy. Therefore, we proposed to recruit 500 male and 500 female participants at baseline which will results in the power of 82% for the moderation analysis based on 50 Monte Carlo simulations.

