### Inclusion criteria

(1) no MDE at baseline, or full remission for 2 months for those who had a past MDE (see below the question). (2) Aged 18 and 65 years. (3) At high risk of MDE based on the depression risk calculators (predicted risk of 6.5%+ for males and 11.2%+ for females) [29], which represent the top two deciles of male and female populations in Canada [29] (4) Agreement to be contacted for follow-up assessments, and (5) no language barriers to English or French. The status of remission will be assessed by the question: “In the past 2 months or longer, has your mood been much improved or back to normal AND you DIDN’T have the symptoms?” This question was adopted from the US NESARC study [30]. Although the risk calculators are sex-specific, our recruitment will be sex and gender inclusive; the recruitment is open to all sexes and genders.

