We acknowledge concerns about the changes in response rates in telephone surveys due to cell phone use and telemarketing. Including eligible participants across the country will enhance the generalizability of the study. Given the vast geographic area of Canada, RDD is the only feasible method. The goal of this study is to recruit participants for a RCT, rather than selecting a representative sample. In an RCT, selection bias is not a serious concern as long as the bias is the same across the intervention and control groups [24]. To mitigate the risk, the telephone survey firm will also access the validated cellphone database. However, the use of cellphone numbers is associated with increased costs. Another potential risk of the proposed study is attrition which may incur selection bias. In previous RCT trial, the response rate at 12-month was 80% in females and 77% in males [33]. As we plan to use the same recruitment and follow-up methods, we anticipate the same response rate in the proposed RCT. Our strategies for reducing attrition will include appropriately designed introductory scripts, a minimum of nine call back attempts spaced over weekdays and times of day and provision of a $25 incentive for each completed interview.

*Knowledge translation (KT).* KT will be in the form of peer reviewed publications, conference presentations and research website dissemination. Only aggregated data will be presented. If the results of this study support the hypothesis, our goal is to implement the coach-guided PDRC in the community as a selective prevention program at Tier 1 and 2 levels through knowledge dissemination and collaboration with key knowledge users, including Public Health Agency of Canada, Mental Health Commission of Canada, Canadian Mental Health Association and mental health units of health regions. We will publish the results of the study in peer-reviewed journals, present at academic and non-academic conferences and symposia, and disseminate the key findings through social media. The authorship of the publications generated from this trial will be determined according to the BMC Medical Research Methodology authorship guidelines. No scientific writers will be used.

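### The female sample size uses 3-month net changes in PHQ-9 prevalence (1.7 and 9.7 points) as 12-month MDE incidences, so the 80% power is not supported for the CIDI primary outcome

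*Protocol article*

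**What the plan says.** Under *Sample size calculation*, the article first reports a pilot with assessments at baseline and 3 months. Its outcome was the proportion of participants with a PHQ-9 score of 15 or more. For women, the proportion in the "female intervention group changed from 12.8 to 14.5" per cent, and that in "the female control group increased from 7.4 to 17.1" per cent. The article prints the net changes as +1.7% and +9.7%. For men it prints -9.5% (intervention) and +1.9% (control).

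The next paragraph begins: "Assuming the 12-month incidence of MDE in female intervention and control groups is 1.7% and 9.7%, respectively". With α = 0.05 and 80% power (printed as β = 0.80), it arrives at 262 women, 131 per arm, and then 330 after allowing for 80% response. The recruitment target of 500 per sex is attributed to the moderation analysis by self-efficacy. No calculation is given for the primary outcome in men.

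Under *Primary and secondary outcome measures*, the primary outcome is the proportion with MDE at 12 months on the 12-month CIDI.

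**The concern.** The planning rates are the pilot's net changes under a new label. A net change in prevalence is new cases minus remissions, so it is not a risk. The horizon changes from 3 to 12 months and the instrument from a PHQ-9 cut-off to a diagnostic interview. The article offers no argument for either step.

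The relabelling affects the result because the variance of a proportion depends on its level. Putting an 8-point gap on a floor of 1.7% makes it look cheaper to detect than the same gap at a higher level. It also implies a risk ratio of 1.7/9.7 = 0.175, an 82% reduction, against a control group that itself receives individualized risk information.

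This is the article's only power statement for the primary outcome. Readers would use it to judge what a null result rules out.

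**Working it through.** **Where the inputs come from**

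- Women, intervention: 14.5 − 12.8 = 1.7 points.
- Women, control: 17.1 − 7.4 = 9.7 points.
- Men, intervention, same metric: 6.2 − 15.7 = −9.5 points. An incidence cannot be negative, so the metric is not an incidence.
- Gap between the female changes: 9.7 − 1.7 = 8.0 points. This splits into the 3-month difference (17.1 − 14.5 = 2.6) and the baseline difference (12.8 − 7.4 = 5.4).

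**The plan's own figure**

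Two proportions, pooled variance under the null, two-sided 0.05, power 0.80:

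n per arm = [1.960 √(2p̄(1 − p̄)) + 0.842 √(p₁(1 − p₁) + p₂(1 − p₂))]² / (p₂ − p₁)²

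With p₁ = 0.017, p₂ = 0.097 and p̄ = 0.057, this is (0.6426 + 0.2718)² / 0.0064 = 130.7, so 131 per arm and 262 in all. Then 262/0.80 = 327.5, close to the stated 330. The arithmetic reproduces. Because 262 is then divided by 0.80, it is a number of completers, although the text places it at baseline.

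**Expected completers**

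The *Discussion* reports that in the previous trial "the response rate at 12-month was 80% in females and 77% in males".

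- Women: 500 × 0.80 = 400, or 200 per arm.
- Men: 500 × 0.77 = 385, about 192 per arm.
- Pooled: 785, about 392 per arm.

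**Power in women under other inputs**

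Power = Φ{[|p₂ − p₁|√n − 1.960 √(2p̄(1 − p̄))] / √(p₁(1 − p₁) + p₂(1 − p₂))}

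| Intervention v control | Basis | n per arm for 80% | Power at 131 | Power at 200 |
|---|---|---|---|---|
| 1.7 v 9.7% | as stated | 131 | 80% | 93% |
| 3.2 v 11.2% | same 8 points, control at the female entry threshold | 163 | 71% | 87% |
| 9.1 v 17.1% | same 8 points, control at the pilot's 3-month level | 279 | 48% | 66% |
| 5.6 v 11.2% | threshold, assumed risk ratio 0.5 | 384 | 37% | 52% |

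The thresholds come from *Inclusion criteria*: "predicted risk of 6.5%+ for males and 11.2%+ for females". The article does not state the horizon of this predicted risk, so using it as a 12-month control risk is an assumption. On that assumption, the planned 9.7% lies below the lowest predicted risk at which a woman can enter. The 17.1% is a 3-month PHQ-9 figure and serves only to show how the level affects power.

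**Detectable at 80% power** (same formula solved for the intervention risk)

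| Group | n per arm | Control → intervention | Difference (points) | Risk ratio |
|---|---|---|---|---|
| Women | 200 | 11.2 → 3.8% | 7.4 | 0.34 |
| Men | 192 | 6.5 → 1.1% | 5.4 | 0.16 |
| Pooled | 392 | 11.2 → 5.65% | 5.55 | 0.50 |

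**The case against.** Four points on the other side deserve weight.

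1. A reader might infer that the 80% power is false, or that the trial is underpowered. The article does not support that. It gives no 12-month CIDI rates by arm, so the true power is unknown, and the calculation is right for its inputs. What can be said is that the power is not supported.

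2. A reader might infer that the wrong inputs set the size of the trial. They did not. They ask for 330 women, while the 500 per sex is attributed to the moderation analysis. The larger number also helps: at 200 per arm, power is 87% for 3.2 v 11.2% and 96% if the implied risk ratio of 0.175 is kept with control at 11.2%. The *Statistical analysis* section says the data are initially analysed by sex, which does not exclude a pooled analysis. Pooled at 392 per arm, 9.1 v 17.1% has 91% power.

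3. It is tempting to put the pilot's 3-month levels, 14.5 v 17.1%, into the formula and report 11% power at 200 per arm, with about 3,090 per arm needed. That case rests on the same 3-month PHQ-9 data that are criticised here. It also includes people already at 15 or more at baseline and ignores the 5.4-point imbalance, whereas the planned model adjusts for baseline PHQ-9. It can show sensitivity at most.

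4. The article never applies the change metric to men for planning. The −9.5 shows why the metric fails and is not a second error.

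All four stand. None of them supplies a reason to read 1.7% and 9.7% as 12-month risks of CIDI MDE.

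**Conclusion.** The point holds as an unsupported planning assumption, not as a calculation error. The only power statement for the primary outcome rests on quantities of the wrong kind, horizon and instrument, and most of the gap between them (5.4 of 8.0 points) comes from the pilot arms' different starting points.

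With the women the trial expects to retain, power ranges from 93% down to 52% over the scenarios shown, and even the favourable ones need large effects. At a control risk equal to the entry threshold, 80% power requires a risk ratio of about 0.34 in women and 0.16 in men.

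These figures assume two-sided 0.05, an unadjusted comparison of two proportions (the method that reproduces the plan's figure) and 80% and 77% follow-up. They also take the thresholds as 12-month control risks. The risk ratio of 0.5 is an assumption. The pooled example uses the female threshold for both sexes, and the pooled control risk could differ.

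**What to change.** Keep N = 1,000 and rewrite the power paragraph:

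- Remove 1.7% and 9.7% as 12-month incidences. If the pilot is kept, describe it as 3-month change in the proportion with PHQ-9 of 15 or more.
- State the 12-month risk difference and risk ratio detectable at 80% power for the expected completers (about 400 women, 385 men, 785 pooled), over a range of control risks labelled as assumptions. The second table gives one example for each group, and the male row fills the present gap.
- Say that taking the eligibility thresholds as control risks assumes a 12-month prediction horizon.
- Leave out 14.5 v 17.1%, or show it only as sensitivity.
- Correct β = 0.80 to power 0.80 (β = 0.20), label the 262 as completers, and reconcile the female intervention change, which appears as both 1.7% and 1.9%.

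The cost is one rewritten paragraph and a less favourable stated power. No extra participants are needed, and the outcome and analysis do not change.

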## Discussion

*Current status.* At the time of submission of this manuscript, we have identified a telephone interview firm who will carry out the recruitment, screening and random selection. The next step will be to program the interview questionnaire into the CATI system. The recruitment is expected to start on November 1st, 2024.

*Potential risk and mitigation strategies.* The recruitment, data collection, and coach guidance will be undertaken via telephone or video. The research staff will not meet the participants in person. Our previous trial showed that providing individualized depression risk does not lead to psychological harms [33]. We will collect data about participants’ mental health. Some participants may feel uncomfortable answering these questions, causing psychological distress. However, we will explicitly inform the participants that participation is voluntary, and they can refuse to answer any questions or withdraw from the study at any time. The data will only be presented, shared, and published in aggregate form. Individuals with an MDE as determined by a diagnostic instrument at the time of screening are not eligible for this study; they will be recommended to seek treatment from health professionals. Through our previous trials [35, 50], we have a protocol in place for helping those who are screened as experiencing ongoing MDE or suicidal behaviours. Our pilot study showed that over 95% of participants in the intervention group agreed to receive the PDRC and the coaching session. Therefore, we do not expect issues in compliance.

We acknowledge concerns about the changes in response rates in telephone surveys due to cell phone use and telemarketing. Including eligible participants across the country will enhance the generalizability of the study. Given the vast geographic area of Canada, RDD is the only feasible method. The goal of this study is to recruit participants for a RCT, rather than selecting a representative sample. In an RCT, selection bias is not a serious concern as long as the bias is the same across the intervention and control groups [24]. To mitigate the risk, the telephone survey firm will also access the validated cellphone database. However, the use of cellphone numbers is associated with increased costs. Another potential risk of the proposed study is attrition which may incur selection bias. In previous RCT trial, the response rate at 12-month was 80% in females and 77% in males [33]. As we plan to use the same recruitment and follow-up methods, we anticipate the same response rate in the proposed RCT. Our strategies for reducing attrition will include appropriately designed introductory scripts, a minimum of nine call back attempts spaced over weekdays and times of day and provision of a $25 incentive for each completed interview.

*Knowledge translation (KT).* KT will be in the form of peer reviewed publications, conference presentations and research website dissemination. Only aggregated data will be presented. If the results of this study support the hypothesis, our goal is to implement the coach-guided PDRC in the community as a selective prevention program at Tier 1 and 2 levels through knowledge dissemination and collaboration with key knowledge users, including Public Health Agency of Canada, Mental Health Commission of Canada, Canadian Mental Health Association and mental health units of health regions. We will publish the results of the study in peer-reviewed journals, present at academic and non-academic conferences and symposia, and disseminate the key findings through social media. The authorship of the publications generated from this trial will be determined according to the BMC Medical Research Methodology authorship guidelines. No scientific writers will be used.

*In summary*, depression is a prevalent and disabling mental illness. Effective self-help can be a way to reduce the risk of depression, which is strongly supported and promoted by the WHO. The proposed study is the first RCT on using coach-guided PDRC to promote effective self-help, if successful, will lead to a novel selective prevention program that is closely aligned with the tiered mental health services model. Our prior research and pilot RCT have shown that the proposed study is highly feasible both methodologically and operationally and has great potential to generate positive results.

## Data Availability

No datasets were generated or analysed during the current study.

## Abbreviations

CATI: Computer assisted telephone interview
GAD: Generalized Anxiety Disorder
ITT: Intention-to-treat
KT: Knowledge translation
MDE: Major depressive episode
MHCC: Mental Health Commission of Canada
MVRP: Multivariate risk prediction
PDRC: Personalized depression risk communication
PHAC: Public Health Agency of Canada
PHQ: Patient Health Questionnaire
PI: Principal investigator
PLE: People with lived experience
RCT: Randomized controlled trial
SPOR: Strategy for patient-oriented research
TSC: Trial steering committee
WHO: World Health Organization
